## Abstract

**Background::**

Total Knee Arthroplasty (TKA) is an intervention that can significantly improve the quality of life of patients with advanced knee osteoarthritis. Early start of rehabilitation and its continuation at home once the patient is discharged are key factors for the success of the process.

This study aims to assess the effectiveness of a home-based telerehabilitation solution (ReHub) on improving functional capacity and clinical outcomes for patients who underwent TKA.

**Methods/design::**

The study is a randomized, open-label with blinded outcome assessor, parallel assignment clinical trial with a sample size of 52 patients that is conducted according to the SPIRIT recommendations. After the TKA intervention, the patients are randomly allocated to the control group or the experimental group with a 1:1 ratio. Both groups follow a Fast Track recovery protocol which includes discharge after 2–3 days from surgery, a daily plan of 5 exercises for autonomous rehabilitation and domiciliary visits by a physiotherapist starting approximately 2 weeks after surgery. The experimental group uses the sensor-based telerehabilitation system ReHub to perform the exercises. The primary outcome measure is the range of motion of the knee. Secondary outcomes include physical performance, quality of life, pain intensity, muscle strength, treatment adherence and satisfaction with the ReHub system. The outcomes assessment is performed at hospital discharge (baseline), at stitch removal (2 weeks after baseline) and 2 weeks after stitch removal (4 weeks after baseline).

The study conforms to the guidelines of the Declaration of Helsinki and was approved by the hospital’s ethics committee.

**Discussion::**

The study will address an important gap in the evidence base by reporting the effectiveness of an affordable and low-cost home-based telerehabilitation solution in patients who underwent TKA.

**Ethics and dissemination::**

The study was approved by the hospital’s ethics committee (“Comité Ético de Investigación Clínica del HCB”, reg. HCB/2019/0571). The trial was registred at ClinicalTrials.gov (NCT04155957). The results of this study will be published in peer-reviewed journals as well as national and international conferences.

**Trial registration::**

NCT04155957 (ClinicalTrials.gov).

**Highlights::**

## Background

Knee osteoarthritis (KO) is the most common joint condition and causes significant amounts of disability worldwide [1]. Total Knee Arthroplasty (TKA) is an intervention which has improved the quality of life of the patients with advanced knee osteoarthritis. In recent years, “Rapid Recovery” or “Fast-Track” strategies, have been developed and applied in TKA and other selective operations. These strategies aim to enhance post-operative recovery and reduce morbidity, functional convalescence and hospital stay lengths and costs [2,3]. Pre-operative rehabilitation and patient empowerment, as well as the early start of post-operative rehabilitation once the patient is discharged, are key factors for the success of the recovery process after a TKA [4,5].

Patients with TKA operated at some hospitals in Spain systematically undergo a specific training program a few weeks before surgery. They familiarize themselves with the surgical process and the physical exercises they shall perform before and immediately after the surgery. This allows for a better recovery and decreases the stress of surgery [6]. After hospital discharge (usually between 48h to 72h after surgery), patients continue the exercise program at home as they have been taught. However, the adherence of the patients to this program is unknown. To monitor patients’ activities, health professionals can only rely on the information provided by the patients themselves and/or their families. Approximately 2 weeks after the surgery, patients start receiving visits from a physiotherapist at home. Domiciliary rehabilitation is estimated to take 10 sessions distributed in 2 or 3 days per week, depending on the availability.

On the other hand, telerehabilitation has been rapidly expanding as an alternative or a complement to conventional face-to-face physical therapy since its development [7]. Telerehabilitation systems monitor the patients with sensors and software, allowing the therapist to intervene in the rehabilitation progress remotely. The patient feels monitored, motivated and supported [8]. Besides, comparable results are obtained to conventional outpatient physical therapy [9,10], or even face-to-face physical therapy with home rehabilitation [11], and are widely accepted by patients [9,10].

Recently Correia et al. [12] demonstrated that home telerehabilitation after TKA is feasible, engaging, and capable of maximizing clinical outcomes in comparison to conventional rehabilitation in the short and medium-term and is far less demanding in terms of human resources.

According to other recent studies, telerehabilitation shows a positive impact on patient compliance and adherence [9,11,13], which is a really important factor for a better functional recovery after TKA surgery. We must not forget the role of these innovative technologies in empowering the patient and promoting their active participation in their recovery process, a vital aspect in achieving maximum success in early and late functional outcomes [14]. It is also important to consider the patient’s opinion on the matter. There is strong evidence to support the use of virtual systems to increase patient satisfaction in patients who have undergone TKA [15]. This trial contributes to the scientific knowledge base regarding the effects of telerehabilitation.

We hypothesized that a home-based telerehabilitation program performed through the remote supervision of the patient’s performance and adherence can improve clinical outcomes compared to conventional (unsupervised) home-based rehabilitation.

Therefore, the overall objective of this study is to evaluate the effectiveness of a new telerehabilitation solution, ReHub, for the improvement of physical function and clinical outcomes following TKA. ReHub is an interactive telerehabilitation system developed by DyCare which delivers personalized home rehabilitation for Muscle-Skeletal Disorder (MSD) sufferers.

## Methods

### Study design and randomization

The study is a prospective, randomized, controlled, parallel-group, open-label with blinded assessor trial that is conducted according to the SPIRIT recommendations [16]. Following informed consent, patients are randomized (with a 1:1 allocation ratio) to a control group or an experimental group. Computer-generated randomization lists are used (using the website www.randomization.com) to sequentially distribute the patients into one of the two groups. The primary outcome measure is knee Range of Motion (ROM).

The study conforms to the guidelines of the Declaration of Helsinki, was approved by the hospital’s ethics committee (“Comité Ético de Investigación Clínica del HCB”, reg. HCB/2019/0571), and registered at the ClinicalTrials.gov website (identifier NCT04155957).

A flow diagram of the study design is shown in ***Figure 1***.

**Figure 1 F1:**
[figure not shown]
REHAPT flow diagram.

### Participants/randomization/allocation/blinding

The general outline of this open-label, parallel-assignment, controlled clinical trial with blinded evaluators is the following: candidates to a TKA with no interfering comorbidities and between 18 and 75 years old will need to sign an Informed Consent Form to be enrolled in the study. The patients then will be randomized with an allocation ratio of 1:1 into one of the two groups: the Control group, receiving the traditional home rehabilitation that patients who undergo Total Knee Arthroplasty (TKA) in a third level hospital (Rapid Recovery Program), or the Experimental group, following the same rehabilitation plan for TKA with ReHub instead of usual autonomous rehabilitation exercices.

Following the allocation of the groups, trained blinded nurses will complete all functional assessments and collect all clinical data on the Case Report Form for each patient. These evaluations will be made at the time of discharge from hospital, after two weeks and after four weeks, both during the follow-up visits.

A total of 52 patients will be recruited following a personal interview carried out by the investigators considering the following inclusion and exclusion criteria mentioned in ***Table 1***.

**Table 1 T1:** Inclusion and Exclusion criteria.

INCLUSION CRITERIA:

1. Age of the candidates shall be between 18 and 75 years 2. Ability to understand and accept the study procedures and to sign an informed consent form 3. Good predisposition to the use of technology or availability of a caregiver providing technological support to the patient 4. Availability to move to the hospital for visits 5. The patient resides in the hospital’s area of influence

**EXCLUSION CRITERIA:**

Any type of disability that could alter the homogeneity of the study leads to exclusion as well as sensory and/or cognitive impairment or concomitant medical conditions which may affect the rehabilitation process. In addition, major medical complications occurring after surgery (e.g. surgical wound infection, suspicious of deep vein thrombosis) also lead to exclusion.

The expected recruitment rate is 2 patients per week.

### Interventions

Patients are normally discharged 48 hours after the operation with an updated physiotherapy schedule and a leaflet containing the exercises and patterns to follow. The physiotherapist makes sure that the patients (from both groups) have understood them and will perform them correctly.

The rehabilitation program duration per patient is 4 weeks (30 days) after hospital discharge. Three visits take place, one at discharge (baseline), another after 2 weeks and the final visit after 4 weeks (***Table 2***).

**Table 2 T2:** Timepoint chart.

	RECRUITMENT	BASELINE VISIT	INTERVENTION (2 WEEKS)	FOLLOW-UP VISIT	INTERVENTION (2 WEEKS)	FINAL VISIT

**TIMEPOINT**	**-t_o_**	**t_0_**		**t_1_**		**t_2_**

Screening & Eligibility	X					

Informed consent procedure	X					

Treatment randomization	X					

ReHub training (Experimental Arm only)			X			

Timed Up-and-Go		X		X		X

Knee ROM		X		X		X

Muscle strength		X		X		X

Pain level (VAS)		X		X		X

WOMAC		X		X		X

EuroQol-5D-5L		X		X		X

Patient diary data collection (Control Arm only)						X

System Usability Scale (Experimental Arm only)						X

Adherence						X

Adverse events				X		X

The following outcome measures are collected for the patients at the visits:

Active Knee ROM (°) with a goniometer, both flexion and extensionPassive Knee ROM (°) with a goniometer, both flexion and extensionTimed Get-Up-and-Go test (s)Quadriceps muscle strength with a dynamometer (kg)Hamstring muscle strength with a dynamometer (kg)Pain Level with a Visual Analog Scale (VAS)Western Ontario and McMaster Universities Osteoarthritis Index (WOMAC)EuroQol-5D-5L scoreAdherence to exercise program (only collected in last visit)System Usability Scale (only collected in last visit for experimental patients)

Both groups shall perform at home the prescribed exercises. The control group will follow the common home rehabilitation recommendations and exercise autonomously while the experimental group patients will use ReHub to perform their exercises; for both groups the exercise pattern will be the same.

In addition, and as part of the usual hospital protocol, during the last two weeks, the participants of both groups will receive a visit from a physiotherapist from an external company, 2–3 days per week, up to 10 sessions. The details of the intervention for each group are as follows:

Experimental Group:A site team physiotherapist will make three home visits during the 4 weeks. In the first visit (the day after discharge), the patient receives a ReHub bag including a tablet with ReHub installed and the Exercise Kit. The site team physiotherapist explains how ReHub works and how to perform exercises. The second visit (second day after discharge) is a follow-up visit to ensure the correct use of ReHub so the patient can perform his/her exercises properly. An optional third visit can be planned for the following day at this stage if the patient has difficulties using the platform. The patient follows the exercise program with ReHub, and a site team physiotherapist monitors the patient’s progress daily through the platform.12–17 days after surgery, the patient attends the hospital for stitch removal and the second visit takes place. If required, in this visit the therapy is reprogrammed. The day after the second visit, a site team physiotherapist makes the last home visit to ensure no problems have arisen during the last 2 weeks.Around 30 days after the surgery, patients attend the hospital for the final control. In addition to the aforementioned outcome measures, patient satisfaction with ReHub is measured by the administration of the System Usability Scale as well.Control Group:The 3 main visits are the same as the experimental group and the same outcomes are measured. The control group does not receive home visits from the site team physiotherapists. Patients are asked to fill out a diary to indicate which exercises they performed and the corresponding dates. At the final visit at the hospital, in addition to collecting the aforementioned outcome measures, the patients’ exercise diary will be collected.

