## Discussion

This study aims to assess the effectiveness of a home-based telerehabilitation program for the improvement of physical function and clinical outcome following TKA.

In addition, patient satisfaction with the telerehabilitation solution (ReHub) is evaluated to explore whether it increases the adherence to the treatment among other improvements. Another important point of the study will be the evaluation of the costs of the rehabilitation process with the ReHub program compared to conventional rehabilitation and as a result, the economic effects it can have, particularly for the public health system.

The randomized controlled design, blinding of the individual performing the outcome assessments, and use of valid tools for the assessment of physical performance and muscle strength (TUG score and dynamometer-based measurements of muscle strength under isometric conditions, respectively) are notable strengths of the study.

However, the short duration of the intervention (4 weeks) and the lack of a long-term follow-up that could help determine with more precision whether telerehabilitation could have lasting benefits could be a limitation to our study. Also, the fact that the adherence of control patients to their exercise program is self-reported in an exercise diary, could affect the evaluation of this parameter.

Notwithstanding these limitations, demonstrating the effectiveness of a home-based telerehabilitation program for physical function and/or muscle strength improvement following TKA could have relevant implications for the post-surgical rehabilitation process. In fact, telerehabilitation solutions could facilitate access and adherence to health interventions, reduce health care costs (associated with supervision, facility provision, and transport of patients), and also contribute to social distancing when it becomes necessary as an infection control action. In addition, the results of the study could support the systematic incorporation of solutions like ReHub in post-surgical rehabilitation protocols, that should be tailored to the individual and collective needs.

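### The ReHub arm alone gets three or four in-person home visits from the site physiotherapist, so the trial estimates a package and cannot credit a difference to ReHub or remote supervision alone

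*Protocol article*

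**What the plan says.** The Background of the protocol article states that "the overall objective of this study is to evaluate the effectiveness of a new telerehabilitation solution, ReHub". Its hypothesis concerns a programme based on remote supervision, and the comparator it names is usual rehabilitation at home, described as unsupervised.

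The section on participants, randomisation, allocation and blinding describes the experimental arm as "following the same rehabilitation plan for TKA with ReHub instead of usual autonomous rehabilitation exercices". The Interventions section adds that "for both groups the exercise pattern will be the same".

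For the experimental arm, the same section then says: "A site team physiotherapist will make three home visits during the 4 weeks". These fall on the first and second days after discharge and on the day after the 2-week hospital visit. One more may be added on the third day if the patient struggles with the platform. At the first visit the physiotherapist hands over the equipment, explains the system and explains how the exercises are done. For the other arm: "The control group does not receive home visits from the site team physiotherapists".

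Two things are common to both arms: a physiotherapist checks at discharge that the patient understands the exercises, and an external company provides home physiotherapy in the last two weeks.

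**The concern.** The objective and the description of the arms point to one difference, ReHub in place of exercising alone. The intervention details show a second: extra in-person time with a site physiotherapist, most of it in the first days at home, when controls have no physiotherapist at home. If the ReHub arm does better, a reader of the objective will credit the sensor system and remote supervision. Some of the gain could come from the visits.

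This matters for how the result is used. The Discussion looks ahead to incorporating systems like ReHub into post-surgical care and to possible savings on supervision. A hospital that adopted the platform without the home visits would be relying on an effect that the trial had not measured. The Discussion's limitations cover the short intervention, the lack of long-term follow-up and the self-reported adherence of controls, but not this imbalance.

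**Working it through.** **1. Reproduce the plan's visit count.** Scheduled site-physiotherapist home visits in the experimental arm (Interventions):
- day 1 after discharge: 1
- day 2 after discharge: 1
- day after the 2-week hospital visit: 1

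The total is 3, as stated. With the optional visit on day 3, 3 + 1 = 4.

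**2. Place the visits against the assessments.** Range of motion is measured at discharge, 2 weeks and 4 weeks (Table 2). The baseline measurement comes before every home visit, so any effect of the visits falls within the post-baseline change.

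| Window | Site home visits, ReHub arm | Site home visits, control | External sessions |
|---|---|---|---|
| Discharge to 2-week assessment | 2 to 3 | 0 | none planned in either arm |
| 2-week to 4-week assessment | 1 | 0 | same provision in both arms |
| Whole 4 weeks | 3 to 4 | 0 | same provision in both arms |

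The Abstract starts the external visits about two weeks after surgery, and stitch removal is 12 to 17 days after surgery. An occasional external session might therefore come before the 2-week assessment. It would be provided to both arms alike, so the difference of 2 to 3 contacts would stand.

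**3. Compare the content.** Both arms are taught the exercises at discharge. Only the ReHub arm has them explained again in person at home, at the first visit. The second visit and the optional one concern use of the platform. The last is a check for problems, which is follow-up and not set-up.

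**4. What the contrast identifies.** Write the between-arm difference as

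D = (effect of ReHub with remote monitoring) + (effect of the extra home visits) + (any interaction).

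Randomisation gives an unbiased estimate of D. No arm receives one component without the other, so D cannot be split. If D were the planned 10°, the data would be equally compatible with the visits contributing nothing or a good part of it. The documents give no figure to narrow this.

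**5. The sample size is unaffected.** With a 10° difference, SD 12°, two-sided 0.05 and 80% power:

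n per arm = 2 × (1.960 + 0.842)² × 12² / 10² = 22.6, rounded up to 23.

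That is 46 evaluable patients, and 46 / 0.9 = 51.1, rounded up to 52. This matches the stated 52, which is the size for detecting D as a whole.

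**6. Why no percentage is given for total contact.** Two to three days a week for two weeks is 4 to 6 external sessions, but the same sentence allows up to 10. The denominator is not fixed, and set-up visits are not equivalent to therapy sessions. The count of 2 to 3 against 0 needs neither assumption.

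**The case against.** The strongest reply is that the visits are how ReHub is delivered. Most of their described content is handing over the kit, explaining the platform and checking its use. Table 2 lists ReHub training as a procedure for the experimental arm only. A sensor system needs training, and controls have no device to be trained on. Remote monitoring and adaptation of the programme are part of what ReHub is, so they are not confounders. Comparing a delivered package with usual care is a legitimate effectiveness design, and the article discloses the visits openly. All of this stands.

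It does not remove the point. The first visit also teaches the exercises, the last is a general check, and the objective and hypothesis do not name in-person visits as part of what is being tested.

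Several stronger readings are tempting but unsupported:
- *The comparison is invalid, or nothing can be credited to ReHub.* Randomisation protects the package comparison, and ReHub is part of that package.
- *Controls get no instruction or physiotherapy.* They are taught at discharge and receive the external sessions.
- *The cost comparison would leave out these visits.* The Discussion announces "the evaluation of the costs of the rehabilitation process with the ReHub program compared to conventional rehabilitation" without saying which items it counts. A condensed article need not list resource-use fields.
- *Three visits contradicts four.* The fourth is optional, and calling it the third at that stage numbers it within the first days. This is loose wording only.
- *Reprogramming happens at the extra home visits.* It is placed at the hospital stitch-removal visit, if required.

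**Conclusion.** The point holds in a limited form. The ReHub arm has 3 to 4 site-physiotherapist home visits against 0, of which 2 to 3 against 0 come before the 2-week assessment. At least one includes exercise instruction beyond what both arms receive at discharge. The trial validly estimates the effect of ReHub with remote monitoring plus these visits. It does not support crediting a difference to ReHub or to remote supervision alone, which is how the objective, the hypothesis and the description of the arms read. Calling the comparator unsupervised is also too broad, since controls have a physiotherapist at home in the last two weeks.

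This rests on the visits being made as described and the external provision being equal in the two arms. How much of any difference in range of motion the visits explain is unknown and could be small. The design and sample size can stay. The stated claim should change.

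**What to change.** - State the objective, hypothesis and planned conclusion as the effect of a package (ReHub with remote monitoring, plus the site-physiotherapist home visits) added to the Fast Track programme, compared with Fast Track alone with external physiotherapy in the last two weeks.
- In the participants section, replace the description of arms that differ only by ReHub with one that names the visits. In the Background, qualify the unsupervised comparator to acknowledge the external sessions.
- Add the unequal in-person contact to the limitations in the Discussion.
- Record for each patient the number of site home visits and external sessions, report them by arm, and count them in any cost comparison. Recruitment was still open when the article was written, so this can be done prospectively for later patients, and from visit records, where kept, for earlier ones.

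The cost is a narrower claim, some rewording and a few data fields. It needs no change to treatment, visits, staffing or sample size.
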